# Efficacy of high-intensity focused ultrasound-assisted hepatic resection (HIFU-AR) on blood loss reduction in patients with liver metastases requiring hepatectomy: study protocol for a randomized controlled trial

**DOI:** 10.1186/s13063-017-1801-2

**Published:** 2017-02-06

**Keywords:** High-intensity focused ultrasound, HIFU, Liver surgery, Hepatectomy, Liver metastasis, Liver transection, Blood loss, Blood transfusion, Randomized trial

## Abstract

**Background:**

Liver resection is the only potentially curative treatment for colorectal liver metastases (LM). It is considered a safe procedure, but is often associated with blood loss during liver transection. Blood transfusions are frequently needed, but they are associated with increased morbidity and risk of recurrence. Many surgical devices have been developed to decrease blood loss. However, none of them has proven superior to the standard crushing technique. We developed a new, powerful intra-operative high-intensity focused ultrasound (HIFU) transducer which destroys tissue by coagulative necrosis. We aim to evaluate whether HIFU-assisted liver resection (HIFU-AR) results in reduced blood loss.

**Methods:**

This is a prospective, single-centre, randomized (1:1 ratio), comparative, open-label phase II study. Patients with LM requiring a hepatectomy for ≥ 2 segments will be included. Patients with cirrhosis or sinusoidal obstruction syndrome with portal hypertension will be excluded. The primary endpoint is normalized blood loss in millilitres per square centimetre of liver section plane. Secondary endpoints are: total blood loss, transection time, transection time per square centimetre of liver area, haemostasis time, clip density on the liver section area, rate and duration of the Pringle manœuvre, rate of patients needing a blood transfusion, length of hospital stay, morbidity, patients with positive resection margin, and local recurrence. Assuming a blood loss of 7.6 ± 3.7 mL/cm^2^ among controls, the study will have 85% power to detect a twofold decrease of blood loss in the experimental arm, using a Wilcoxon (Mann-Whitney) rank-sum test with a 0.05 two-sided significance level. Twenty-one randomized patients per arm are required. Considering the risk of contraindications at surgery, up to eight patients may be enrolled in addition to the 42 planned, with an enrolment period of 24 months. Randomization will be stratified by surgeon.

**Discussion:**

We previously demonstrated the safety and efficacy of intra-operative HIFU in patients operated on for LM. We also demonstrated the efficacy of HIFU-AR in a preclinical study. Participants in the HIFU-AR group of this randomized trial can expect to benefit from reduced blood loss and decreased ischemia of liver parenchyma.

**Trial registration:**

Clinicaltrial.gov, NCT02728167. Registered on 22 March 2016.

**Electronic supplementary material:**

The online version of this article (doi:10.1186/s13063-017-1801-2) contains supplementary material, which is available to authorized users.

## Background

### Medical and scientific context

Patients with most solid tumours may develop liver metastases (LM). However, LM occur mainly in patients with colorectal cancer (CRC). In France, CRC is the second most frequent cancer, with an incidence of nearly 41,000 cases each year. It continues to have a poor prognosis and causes nearly 16,000 deaths per year, often due to LM. Hepatic resection is the mainstay of treatment for LM and remains the only potentially curative intervention.

Unfortunately, LM resections are complex major procedures and the resulting blood loss may be significant, leading to the requirement for blood transfusions during the procedure. Such transfusions are correlated with increased morbidity, mortality and risk of tumour recurrence [1–4]. Therefore, the control of blood loss is mandatory to limit morbidity, mortality and recurrence.

Since the hepatic parenchyma tolerates ischemia better than bleeding, intra-operative manœuvres have been proposed to minimize the risk of bleeding during hepatic resection. These include total vascular exclusion, the Pringle manœuvre and selective ligature to control hepatic inflow [5–10]. None of these methods is universally practical or completely effective, and each carries a risk of inducing liver dysfunction in patients with chronic liver disease. Vascular clamping is a time-critical technique, since the risk of morbidity is increased if clamping lasts more than 60 continuous minutes.

### Overview of high-intensity focused ultrasound (HIFU)

HIFU is mechanical waves generated by an ultrasound transducer. As with conventional ultrasound, HIFU can propagate harmlessly through living tissue. However, if the ultrasound beam carries sufficient energy and is brought into a tight focus, the energy within the focal volume can cause a local rise in temperature of sufficient magnitude (up to 80 °C) to generate irreversible cell death. This occurs in a few seconds through coagulative necrosis without damaging the surrounding tissue.

HIFU offers several advantages, which encourage its clinical development. First, HIFU allows non-invasive real-time targeting using sonography. Such real-time monitoring enables adjustment of treatment plans. Second, the mechanism of action of HIFU is not tumour-specific; therefore a wide range of tumour types can be targeted. Third, HIFU is mechanical waves, therefore there is no ionizing radiation. Treatment can be given more than once, as there is no upper limit of tissue tolerance to repeated ultrasound exposure. Finally, HIFU generates very few side effects, and serious adverse events are rare [11]. In several centres worldwide, HIFU has been in clinical use for 5 to 10 years, sometimes in daily practice, to treat solid tumours (both malignant and benign), including those of the prostate [12], liver [13, 14], breast [15] and kidney [16]. Current data are encouraging and the role of HIFU in oncology is likely to expand as devices become more widely available.

However, several technical limitations of currently available HIFU devices have been raised, such as the long time needed to treat tumours of several cubic centimetres. For example, the sonication time (defined as the time from the first to the last sonication) to ablate abdominal pathologies such as uterine leiomyomas with target volumes of 4.6 cm^3^ ranged from 32 to 135 minutes [17, 18]. The use of an extracorporeal HIFU device is clinically feasible for the treatment of hepatocellular carcinoma [13, 19] but only a small part (approximately 30%) of the liver is accessible using a non-invasive HIFU device. In addition, phase aberration and liver movements can produce secondary lesions (such as skin burns or gastric lesions) if a completely extracorporeal treatment is performed. To fill these technical gaps, we undertook a research program on CRC LM treatment by HIFU.

### The HIFU toroidal device: intra-operative HIFU prototype

We previously developed a toroidal HIFU transducer that enables the destruction of large volumes of tissue over short periods of time [20]. This work led to the development of a prototype that has been tested in vitro and in preclinical studies. These studies demonstrated the safety and efficacy of treating the liver using HIFU generated by a toroidal transducer [21–26]. A collaboration with the EDAP TMS company has allowed a prototype to be developed for clinical use and this is currently being evaluated for the treatment of colorectal LM [27].

The HIFU probe is brought into contact with the liver using a sterile ultrasound cooling and coupling liquid (Ablasonic®, EDAP TMP, Vaulx en Velin, France) contained in a sterile polyurethane envelope (Civco, Kalona, IA, USA). It is possible to change the location of the focal zone by adjusting the quantity of coupling liquid between the device and tissues or by electronic focusing. Under these conditions, the focal zone can be placed anywhere between the surface of the liver and 9 cm in depth. This allows treatment of the entire plane of liver transection. A 7.5 MHz ultrasound imaging probe (Vermon, Tours, France) is placed in the centre of the device and connected to a BK HAWK 2102 EXL scanner (BK Medical, Herlev, Denmark) to guide the liver resection. Specific software is used to define the treatment zone from a two-dimensional ultrasound image. The user interface displays the position of the HIFU-treated region superimposed on the sonogram obtained by the integrated ultrasound imaging probe. It is therefore possible to locate the ablation and visualize in real time the treated zone created during ultrasound exposures.

### Previous clinical results

Our team has already demonstrated the safety and feasibility of HIFU for intra-operative ablation of liver parenchyma. We have also demonstrated in an animal study that HIFU can be used to assist hepatic resection.

The HIFU device using a toroidal HIFU transducer guided by ultrasound imaging was evaluated clinically for the treatment of colorectal LM during an open procedure. The transducer has a toroidal shape with a diameter of 70 mm and is divided into 256 emitters each of 0.13 cm^2^. The radius of curvature is 70 mm to enable treatment of the deepest regions of the liver. The operating frequency is 3 MHz.

We conducted a prospective, single-centre phase I–IIa trial [27]. HIFU was delivered immediately before scheduled hepatectomy. To demonstrate the safety and efficacy of rapidly ablating large liver volumes, ablations were performed on healthy tissue within the areas scheduled for resection. In total, 30 ablations (one superficial and one at least 1 cm deep) were carried out in 15 patients. These ablations were all generated within 40 seconds and on average measured 27.5 × 21 mm. The phase I element of the study (n = 6) showed that use of the HIFU device was feasible and safe, and did not damage neighbouring tissue. The phase IIa study (n = 9) showed both that the area of ablation could be precisely targeted on a previously implanted metallic mark and that ablations could be undertaken deliberately to avoid such a mark. Ablations were achieved with a precision of 1–2 mm.

These results enable us to conduct a randomized phase II trial to evaluate whether HIFU-assisted liver resection (HIFU-AR) reduces blood loss compared to standard liver resection in patients with LM.

## Methods/Design

### Objectives

The primary objective is to compare the blood loss during hepatectomy in patients treated by HIFU-AR (arm A) versus standard liver resection (arm B).

The primary endpoint is normalized blood loss in millilitres/square centimetres, defined as total blood loss (in millilitres) divided by the resected hepatic surface (in square centimetres). Total blood loss will be measured during the whole liver transection procedure, i.e. between beginning the section of liver parenchyma and the end of resection including complete haemostasis of the raw surface of the remaining liver. In arm A, time needed to perform HIFU pre-coagulation will be added to this duration. Of note, blood loss is systematically determined by weighing all blood-soaked surgical mops (PB1502, Mettler Toledo, Columbus, OH, USA) and the aspirated fluid (blood suctioned out of the abdomen) on a high-precision scientific scale.

In both arms, the secondary endpoints are:transection time (minutes) defined as the time required to achieve the liver transection (minutes) and the transection time per surface of resected liver area (minutes/square centimetres);haemostasis time (minutes), defined as the time lapse between the end of transection until completion of haemostasis (minutes);clip density on the section area, defined as the total number of haemostatic clips used to perform haemostasis on the liver section area divided by the raw surface of the remaining liver (in square centimetres) (number of clips per square centimetre of liver area);rate and duration of the Pringle manœuvre, defined as the number of patients requiring Pringle’s manœuvre during the operating procedure [if blood loss > 500 mL during the transection, measured through the suction device, the surgeon will be authorized to perform a hepatic pedicular clamping (Pringle’s manœuvre)];rate of patients needing a blood transfusion, defined as the number of patients requiring blood transfusions either during the operation or after it (per-operative transfusion will be required for patients with blood loss > 1000 mL; post-operative transfusion will be required if Hb <8 g/dL or 10 g/dL if previous history of coronary disease or stroke);duration of hospital stay (days), calculated from D_0_ (date of surgery) to the end of hospitalization post-surgery;safety and tolerability assessed using the Dindo-Clavien classification specific to surgical complications. During the first 10 days after surgery, we will collect data on haemoglobin, platelets, alanine amino-transferase (ALT), aspartate amino-transferase (AST), gamma-glutamyltransferase (GGT), prothrombin time (PT) and total bilirubin values;the proportion of patients with malignant tumours who have a positive resection margin and patients with local recurrence (from randomization to M_6_).

### Study design

This is a prospective, single-centre, randomized, comparative, open-label, phase II study to evaluate the efficacy and the safety of HIFU-AR, using the device described, during an open liver resection in patients with LM.

Patients will be randomized 1:1 to either:arm A (experimental arm): pre-coagulation by HIFU-AR plus standard surgical liver resectionarm B (control arm): standard surgical liver resection.

The randomization will be performed via an Internet platform in the operating room and will be stratified by surgeon ([name]) to ensure equal allocation of subgroups of participants (i.e. to each surgeon) in each arm.

The flowchart is represented in Fig. 1. The Standard Protocol Items: Recommendations for Interventional Trials (SPIRIT) checklist can be found in Additional file 1.

**Fig. 1 Fig1:**
[figure not shown]
CONSORT flowchart

### Study population

Inclusion and exclusion criteria are listed in Table 1.

**Table 1 Tab1:** Inclusion and exclusion criteria

Inclusion criteria	Exclusion criteria
Age ≥ 18 years	History of previous major hepatic surgery (i.e. more than three liver segments) or biliary major surgery (except gall-bladder surgery by laparoscopy if more than 6 months previously)
Patients with liver metastases requiring a hepatectomy of ≥ 2 segments	Patients with cirrhosis or sinusoidal obstruction syndrome with portal hypertension
Eastern Cooperative Oncology Group performance status ≤ 1	Pregnant women
Adequate bone marrow and liver function at baseline (defined by platelet count ≥ 100 × 10^9^/L, and haemoglobin of ≥ 9 g/dL, and total bilirubin ≤ 1.5 × upper limit of normal, and transaminases ≤ 5× upper limit of normal)	
Recovered from prior anti-neoplasic treatment-related toxicity (grade <2 persistent treatment-related toxicity as per Common Terminology Criteria for Adverse Events v4 are accepted	
Willingness for follow-up visits	
Covered by a medical insurance	
Signed and dated informed consent indicating that the patient has been informed of all aspects of the trial prior to enrolment	

### Study medical device

The study device is the HIFU prototype from the EDAP TMS company. Currently, this device has no CE mark and is restricted to clinical trials.

The HIFU system is composed of three parts:a sterilisable probe, manually brought into contact with the liver, and its accessories (sterile envelope and O-ring seal);a treatment module including electrical signal generation and treatment control systems. HIFU exposures are activated using a foot pedal.LivKit: single-use consumable

A sterile envelope (Civco #610-542) is placed around the probe to create a reservoir that will be filled by a liquid (Ablasonic®; EDAP TMS, Vaulx-en-Velin, France) ensuring ultrasonic coupling and the transductor’s cooling. The O-ring seal keeps the balloon in place and ensures the reservoir is sealed. The single-use LivKit is installed on the HIFU system before each treatment. During treatments, the transducer is cooled using a continuous flow of Ablasonic® at 10 °C at a rate of 0.3 L/min. A peristaltic Masterflex pump (L/S model 7518; Cole-Parmer Instruments Co., Chicago, IL, USA) drives the water around the closed cooling circuit of the Livkit.

The LivKit contains:350 mL of Ablasonic®One set of flexible pipes

### Surgical procedure

Anaesthesia will be performed according to standard procedure. Central venous pressure (CVP) will be measured immediately before and after the transection. No pharmacological intervention (such as a diuretic) and no surgical procedure (such as infra-hepatic inferior vena cava clamping) will be used to modify the CVP.

The procedure begins with a full exploration of the abdominal cavity, liver palpation and intra-operative ultrasound to confirm the indication of liver resection. Hepatectomy will be carried out in the same way in the two study arms. In arm A, hepatectomy will be performed after pre-coagulation of the hepatic parenchyma by HIFU along the section plane. This will be the only difference between arm A and arm B. Whenever possible, selective control of inflow will be performed. Otherwise, the Pringle manoeuvre will be used if haemorrhage of more than 500 mL occurs during hepatectomy.

In arm A, pre-coagulation is intended to establish a defined full-thickness plane of coagulative necrosis. This is generally achieved by six to ten side-by-side 40-s HIFU ablations, though more can be used if necessary. Resection is performed in the middle of the pre-coagulated zone.

In both arms, parenchymal division will begin along line marked by electrocautery and then cut with scissors. Liver resection technique (the same for both groups) uses a Kelly clamp claw, a suction device, a bipolar forceps and metallic clips. Blunt clamp dissection is a rapid, easy and cheap method. In essence, a large Kelly clamp is used to crush the liver parenchyma. The relatively soft liver substance dissects away, leaving behind the vascular and biliary structures, which are then ligated by vascular clips.

In arm A, it is planned that all vessels < 5 mm in diameter are sealed successfully using HIFU pre-coagulation and will not require any additional haemostasis. Surgical clips will be used only to control the few vessels > 5 mm in diameter.

After completion of liver parenchyma section and removal of the resected liver, the surgeon will complete haemostasis of the raw surface of the remaining liver. This haemostatic phase will be performed only with Prolene® stitches (Ethicon Inc., Cornelia, GA, USA), or coagulation with electrocautery, bipolar forceps or Argon beam coagulator.

Any use of special haemostatic products [such as Tachosil® (Takeda Pharmaceutical Company Limited, Osaka, Japan) or biological glue] will be noted.

Blood loss volume during this phase of haemostasis will be measured and added to the previous blood loss (during the transection phase) for evaluation of the primary endpoint.

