#### Statistical analyses

Qualitative variables will be described using frequency and percentage distributions. The number of missing data will be given, but will not be considered for the calculation of proportions.

Quantitative data will be described using the number of observations, mean, standard deviation, median, minimum and maximum values.

Patient characteristics and other baseline data (demographics, disease characteristics, clinical and biological data) will be summarized. The date of randomization will serve as a reference for calculation of durations unless otherwise indicated.

All analyses will be performed using the SAS software v9.1 (SAS Institute Inc., Cary, NC, USA).

The primary endpoint will be analysed for the ITT and PP populations.

A Wilcoxon (Mann-Whitney) rank-sum test will be used to compare the normalized blood loss distribution between the two arms at a 5% level in a two-sided situation.

For secondary endpoints, data will be compared between the two arms using a Wilcoxon (Mann-Whitney) rank-sum test. The rate of positive margin and the rate of local recurrence will be summarized by a proportion together with their 95% confidence interval. Post-operative complications will be described by study arm and compared using a Pearson’s chi^2^ test or a Fisher’s exact test, if adequate.

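### Arm A alone is given a size limit for clip use while HIFU is called the only difference between arms, so the clip-density comparison cannot separate vessel sealing from adherence to that sentence

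*Protocol article*

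**What the plan says.** All the text is in the Protocol article.

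- **Surgical procedure, on the comparison.** Of HIFU pre-coagulation along the section plane it says: "This will be the only difference between arm A and arm B". It describes a single resection technique for both groups and lists metallic clips among its tools.
- **Surgical procedure, on clips in general.** Crushing the parenchyma works by "leaving behind the vascular and biliary structures, which are then ligated by vascular clips". No diameter limit is given.
- **Surgical procedure, on clips in arm A.** "In arm A, it is planned that all vessels < 5 mm in diameter are sealed successfully using HIFU pre-coagulation", and these vessels are not expected to need further haemostasis. The next sentence reads: "Surgical clips will be used only to control the few vessels" above 5 mm in diameter. Nothing comparable is written for arm B.
- **Objectives.** A secondary endpoint in both arms is clip density, "the total number of haemostatic clips used to perform haemostasis on the liver section area divided by the raw surface of the remaining liver".
- **Statistical analyses.** "For secondary endpoints, data will be compared between the two arms using a Wilcoxon (Mann-Whitney) rank-sum test".
- **Study design; Data collection and follow-up.** The trial is open-label, and intra-operative measures are excepted from blinded assessment.

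**The concern.** An endpoint can show what a device does only if the arms are otherwise handled by the same rule for that endpoint. Here the number of clips is the outcome, and the text on when to place a clip differs by arm. The surgeon knows the allocation and decides whether to place each clip.

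At stake is the interpretation of one tested secondary endpoint. A significant reduction in clip density would naturally be read as evidence that HIFU seals small vessels, and the article names a multicentre phase III study as the next step. The arm A sentence also conflicts with the claim that pre-coagulation is all that separates the arms.

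**Working it through.** **1. The passages side by side.**

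| Topic | Both arms | Arm A only |
|---|---|---|
| Technique | the same, clips included | – |
| What is clipped | structures left after crushing, no size limit | only vessels above 5 mm |
| Stated difference | pre-coagulation alone | pre-coagulation, plus the clip sentence |

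If the arm A sentence is an instruction, there are two differences between the arms. If it is a forecast, there is one, but the text does not say so.

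**2. Why the two explanations cannot be separated.** Simplify by letting arm B clip every structure left after crushing, and define:

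- s = share of arm B clips that go on vessels below 5 mm
- u = share of those small vessels left unsealed by HIFU in arm A
- c = share of the unsealed small vessels that the surgeon clips in arm A

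The ratio of clip density, arm A to arm B, is then

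f = 1 − s(1 − u·c).

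Only the product u·c enters. Take s = 0.25 as an example:

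- HIFU seals every small vessel (u = 0): f = 1 − 0.25 × (1 − 0) = 0.75.
- HIFU seals none (u = 1) and the sentence is followed to the letter (c = 0): f = 1 − 0.25 × (1 − 0) = 0.75.

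The result is the same from opposite device performance. With c = 1, the expectation reading, f = 1 − s(1 − u) and the difference does measure sealing.

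**3. How often the wording alone could give a significant test.** The protocol has no clip-density figure, so there is nothing to reproduce, and this step is illustration only. Its assumptions are not in the document: log-normal clip density, coefficient of variation (CV) 0.4 to 1.0, HIFU sealing nothing, and arm A clipping a fraction f of what arm B clips. From the Sample size section come 21 patients per arm; the test is Wilcoxon, two-sided at 5%. With 10,000 simulated trials per cell, the percentage significant is:

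| CV | f = 1 | 0.9 | 0.75 | 0.5 | 0.25 |
|---|---|---|---|---|---|
| 0.4 | 4.6 | 13.3 | 62.5 | 100.0 | 100.0 |
| 0.6 | 5.2 | 8.5 | 35.8 | 96.9 | 100.0 |
| 0.8 | 4.6 | 6.9 | 24.2 | 85.4 | 100.0 |
| 1.0 | 4.8 | 6.6 | 18.9 | 73.0 | 99.9 |

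The answer runs from the nominal 5% to certainty, depending on a fraction that the protocol does not give.

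**4. What is untouched.** The planned size concerns blood loss only. With control mean 7.6, SD 3.7 and a halving to 3.8, P = Φ(3.8 / (3.7 × √2)) = 0.766. Noether's formula gives N = (1.960 + 1.036)² / (12 × 0.25 × 0.266²) ≈ 42, or 21 per arm, as stated.

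**The case against.** The strongest reply is that the arm A sentence is a consequence and not a rule. It directly follows the statement that smaller vessels should already be sealed, and the technique is said to be common to both groups. On that reading, any structure still needing control is clipped in either arm, HIFU changes how many there are, and fewer clips is a genuine result. This reading is open and cannot be excluded. But the sentence is worded as a restriction, is addressed to unblinded surgeons and has no arm B counterpart, so the text does not settle the matter. Nor is this detail left to a fuller document, since the article itself contains both statements.

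Three stronger inferences are tempting, and the document does not support them.

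- **That a difference is built in, so the endpoint can show no device effect.** Nowhere are surgeons told to leave a bleeding small vessel unclipped. Even with an arm-specific rule, a comparison of clip use between two strategies is valid; what is limited is attribution to sealing.
- **That the rule biases blood loss in favour of arm A.** Blood is measured until haemostasis is complete, so bleeding from unsealed, unclipped vessels would count against arm A. An effect on transection time is conceivable but not quantified.
- **That clips are counted in a phase that uses none.** The later haemostatic phase relies on stitches and coagulation, but the endpoint counts the total number of clips on the section area and is not confined to that phase.

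**Conclusion.** The point holds as a conflict within the Surgical procedure section that leaves a tested secondary endpoint partly set by arm-specific wording. A lower clip density in arm A would not by itself show that HIFU sealed the smaller vessels.

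The size is unknown. It depends on the share of clips placed on vessels below 5 mm and on how literally surgeons take the sentence, and the protocol gives neither. The simulation shows that a material effect is possible; it does not show that one will occur. The matter is confined to clip density and to the accuracy of the statement about the only difference. It should be corrected, but it does not threaten the trial's main conclusion.

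**What to change.** Reconcile the clip passages by stating which of two things the arm A sentence is. The clinical rule itself is for the sponsor and investigators to decide.

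- **An expectation.** Say so, and state that the same clip criterion applies in both arms. The planned test can stay, with the caveat that clips are placed and counted unblinded.
- **An arm-specific instruction.** Describe it as part of the HIFU-AR strategy and correct the statement that pre-coagulation is the only difference. Report clip density by arm descriptively, without a test or an efficacy claim about sealing, next to the special haemostatic products whose use is already to be noted.

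The cost is a few sentences of protocol and analysis wording. Under the second option one secondary endpoint loses its p-value. Sample size and the primary analysis do not change.
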